# Effects of progressive intensity resistance training on the impact of fibromyalgia: protocol for a blinded randomized controlled trial

**DOI:** 10.1186/s12891-023-06952-3

**Published:** 2023-10-14

**Keywords:** Fibromyalgia, Chronic Pain, Exercise, Quality of life

## Abstract

**Background:**

Fibromyalgia guidelines indicate that exercise is critical in the management of fibromyalgia, and there is evidence that patients with fibromyalgia can perform resistance training at moderate and high intensities. However, despite the biological plausibility that progression of intensity provides greater benefit to individuals, no studies have compared different intensities (progressive versus constant intensities) of the same exercise in this population.

**Objective:**

To compare the effect of 24 sessions of resistance training (progressive vs. constant intensity) on impact of fibromyalgia, sleep quality, anxiety, depression, pain, walking ability, and musculoskeletal capacity.

**Methods:**

A protocol for a blinded randomized controlled trial. The sample will be randomized into three groups: group 1 (progressive intensity, experimental), group 2 (constant intensity, control A), and group 3 (walking, control B). Group 1 will perform resistance training at moderate intensity (50% of maximum dynamic strength), previously determined by the 1 repetition maximum (1-RM) test in the proposed exercises. The strength of each individual will be reassessed every 4 weeks (by 1-RM) and the intensity of each exercise will be positively adjusted by 20% of the value observed in kg (i.e., first month 50%; second month 70%; third month 90% of the maximum dynamic strength). Group 2 will perform the same procedure, but the intensity will be maintained at 50% of the maximum dynamic strength throughout the treatment (i.e., constant intensity from the first to the third month). Group 3 will perform a 40-minute treadmill walk at low intensity, defined by a walking speed corresponding to 60-70% of the maximum heart rate, which we will control with a heart rate monitor. All groups will receive a 45-minute pain education session prior to the exercise program, covering the pathophysiologic mechanisms of chronic pain, strategies for coping with pain, avoiding hypervigilance, and deconstructing beliefs and myths about chronic pain.

**Discussion:**

The results of the present study may help health care professionals adjust the intensity of resistance training and thus plan the most effective intervention (progressive or constant intensity) to reduce the impact of fibromyalgia on patients’ lives.

**Trial registration:**

Brazilian Registry of Clinical Trials (ReBEC) ID: RBR-9pbq9fg, date of registration: October 06, 2022.

## Introduction

Fibromyalgia is a chronic condition characterized by widespread pain and complex symptoms, including fatigue, sleep disturbance, autonomic dysfunction, mood disturbance, and functional symptoms (those not explained by structural changes) [1, 2]. The prevalence varies from 2 to 6% in the world population and is more prevalent in women aged 20 to 55 years [3].

Treatment recommendations are divided into pharmacologic and nonpharmacologic [4]. Pharmacological interventions include drugs with neurological (amitriptyline, duloxetine, milnacipran, pregabalin), analgesic (tramadol), and muscle (cyclobenzaprine) effects. Nonpharmacologic interventions focus on physical therapies (acupuncture, hydrotherapy), meditative (qigong, yoga, tai chi, mindfulness), cognitive-behavioral, and physical exercise (aerobic and/or resistance training) [4].

Exercise-induced analgesia has been postulated to occur through several mechanisms: reduction of anti-inflammatory cytokines [5]; regulation of the release of some neurotransmitters that may be reduced in people with chronic pain (e.g., serotonin [5], dopamine, and norepinephrine) [6]; and cortical reorganization [7]. However, exercise-induced analgesia may not occur (or occur in a dysfunctional manner) in people with chronic pain [5, 8, 9], which may affect these patients’ adherence to treatment [9–11].

Some systematic reviews have examined different types of exercise in patients with fibromyalgia, such as flexibility [12, 13], mixed [14], resistance training [1, 2], aquatic [15], and aerobic [16]. For example, resistance training is known to be more effective than flexibility (on pain and physical function) [17], and aerobic exercise (e.g., walking) is one of the most referenced in the literature [16]. However, studies do not provide details on the appropriate procedure for adjusting the intensity of resistance training.

Evidence-based practice suggests that we should follow a tripod for health interventions: scientific evidence, professional knowledge, and patient preference [18, 19]. In this context, Andersson et al. [20] found that women with fibromyalgia prefer resistance exercises with adjusted intensity using free weights (i.e., resistance training), because the higher the load in kg (intensity) used to resist the movement, the shorter the time under muscle tension, and consequently the lower the level of stress and muscle fatigue (during and after exercise). High-intensity resistance training is also safe for people with fibromyalgia [17, 21].

However, only two systematic reviews have examined this scenario [18, 21]. The first study [17] suggests that resistance training at moderate or high intensity improves physical function in women with fibromyalgia. The second study [21] suggests the frequency (twice a week), intensity (40–80% of maximum dynamic strength), volume (1 to 2 sets of 4 to 12 repetitions of the movement), and target muscle group (gastrocnemius, quadriceps, hamstrings, pectorals, latissimus dorsi, rhomboids, deltoid, biceps, and triceps).

It is important to note that although exercise has not been shown to increase pain during its performance [22], muscle contraction can cause pain [23], and greater exercise intensity can elicit greater pain sensations, which may interfere with treatment adherence [24]. An alternative to reduce this side effect is to progressively increase exercise intensity, with loads gradually added according to biological adaptations [25]. Some studies have used this strategy in patients with fibromyalgia [22, 26–28], but the results are controversial [27–32] and the comparison between groups did not control for the progression of exercise intensity [27–32]. Studies that have used progressive intensity resistance training in patients with fibromyalgia have found reductions in disability [29] and fatigue [30].

However, the same comparison between intensities (progressive vs. constant) has not yet been performed in research on fibromyalgia, which leads to the question: does resistance training with progressive intensity, compared to constant intensity (on walking and resistance training), promote a greater reduction in the level of fibromyalgia impact? The answer to this question will characterize the scientific and social feedback of this research, which will provide subsidies to health professionals to adjust the intensity of resistance training and thus plan the most effective intervention (progressive or constant intensity; walking or resistance training) to reduce the impact of fibromyalgia in the lives of the patients.

The hypothesis is that progressive intensity resistance training in patients with fibromyalgia will produce a greater reduction in impact of fibromyalgia than constant intensity exercise (walking and resistance training). Thus, the aim of the study is to compare the effect of 24 sessions of resistance training (progressive intensity vs. constant-intensity) on impact of fibromyalgia after 24 sessions of resistance training, as well as the global perceived effect regarding treatment and impact of fibromyalgia during the intervention and after 3 months of non-exercise follow-up.

## Methods

### Trial design

This is a protocol for a blinded randomized controlled trial reported according to the Standard Protocol Items Recommendations For Interventional Trials [33]. We used the Template for Intervention Description and Replication [34] to describe the proposed intervention.

### Ethics

The research will be conducted at the Federal University of São Carlos. All procedures of this project have been approved by the Ethics Committee for Human Research of the aforementioned institution (report number: 5.499.078) and by the Brazilian Registry of Clinical Trials (ReBEC), under number RBR-9pbq9fg (available at: https://ensaiosclinicos.gov.br/rg/RBR-9pbq9fg), date of registration: October 06, 2022. We will publicize the research through social media (WhatsApp®, Facebook®, Instagram®, Twitter®) and through the University’s means of dissemination, in addition to brochures and posters in public health services in the city of São Carlos.

### Participants and settings

We will recruit individuals between the ages of 20 and 55 (which will provide greater external validity) to participate in the research through free, prior, and informed consent. Inclusion criteria: I) Diagnosis of fibromyalgia according to the recommendations of the American College of Rheumatology [35]. Non-inclusion criteria: (I) neurological conditions that would interfere with the assessments, such as paralysis, major sensory changes, and level of consciousness/understanding; (II) advanced joint disease; (III) suspected thrombosis, heart disease, and immediate postoperative period; (IV) pregnancy; (V) abuse of alcohol and illicit substances; (VI) active cancer.

### Sample size

We performed the sampling using Ene 3.0 and G*Power 3.1.9.7 software, considering the comparison of three independent groups (progressive intensity [n = 21]), group 2 (constant intensity [n = 21]), and group 3 (walking [n = 21]) at four different stages (before, during the intervention, after 24 exercise sessions, and 3 months after the end of treatment) by ANOVA for repeated measures. We chose impact of fibromyalgia as the primary outcome variable, measured by the Revised Fibromyalgia Impact Questionnaire (FIQ-R). We based the calculation on detecting the minimum clinically important difference of 27 points between independent groups (Ene) [36], standard-deviation of 16.3 points (Ene) [37], statistical power of 95% (G*Power), significance of 5% (both), effect size of 0.41 (G*Power) [38, 39], and sample loss of 15% (Ene). Thus, the sample must contain 21 individuals per group (total = 63).

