### Statistical analysis

We will perform statistical analysis based on intention-to-treat analysis. We will use histograms and normality tests to verify the distribution of the data. Comparisons will be made through mixed linear models using interaction between factors time (before, during the intervention, after 24 exercise sessions, and 3 months after the end of treatment) and group (progressive intensity, constant intensity, and walking), besides, the baseline will be used as a covariate in the analyses [75]. Data will be presented as mean, standard-deviation, difference between means, confidence interval (95%) of these differences, and effect size (Cohen d). We will consider a significance level of 5% on the SPSS® software, version 17.0 (Chicago, IL, EUA) [76].

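### The 21 per group rests on two calculations that do not agree, and on the most likely reading the 63 contains no allowance for the stated 15% loss

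*Protocol article*

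**What the plan says.** The Sample size section of the protocol article names two programs: "We performed the sampling using Ene 3.0 and G*Power 3.1.9.7 software". The design is "considering the comparison of three independent groups", "at four different stages (before, during the intervention, after 24 exercise sessions, and 3 months after the end of treatment", analysed "by ANOVA for repeated measures". Most inputs are tagged with a program. To Ene belong the 27-point difference on the FIQ-R, the SD of 16.3 and the 15% loss. To G*Power belong the power and the effect size: "statistical power of 95% (G*Power), significance of 5% (both), effect size of 0.41 (G*Power". A single result follows: "sample loss of 15% (Ene). Thus, the sample must contain 21 individuals per group (total = 63".

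The section does not say which repeated-measures effect is tested (between groups, within subjects or interaction), nor what correlation between visits was assumed. The Randomization section prepares 63 envelopes, so no reserve is added later.

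The Statistical analysis section plans something else: "Comparisons will be made through mixed linear models using interaction between factors time" and group, with baseline as a covariate. The Outcomes section makes the primary outcome the effect on fibromyalgia impact after 24 sessions, progressive against constant intensity.

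**The concern.** One conclusion is drawn from two sets of inputs, and the loss allowance sits with the set that cannot have produced the answer. If 21 per group came from G*Power alone, the stated 15% was never added and the 95% applies only if nobody is lost. The two sets also assume very different effects, so a reader cannot tell what difference the trial is powered to detect.

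This bears on how the result is read. The Discussion says that if the exercises do not differ significantly, patients may choose among them by preference. A null result supports that only as far as the trial could have detected a smaller difference.

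**Working it through.** **Inputs.** From the Sample size section: k = 3 groups, m = 4 visits, f = 0.41, alpha 5%, power 95%; difference 27 points, SD 16.3, loss 15%. Assumptions not in the document: the between-groups main effect as the G*Power test, a correlation ρ = 0.5 between visits (taken as the software default), and two-sided tests for two means.

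**1. Reproducing the 63.** For the group main effect, the noncentrality is λ = N·f²·m / (1 + (m − 1)ρ), with degrees of freedom k − 1 and N − k.
- N = 60: λ = 60 × 0.1681 × 4 / 2.5 = 16.14, power 94.8%.
- N = 63: λ = 63 × 0.1681 × 4 / 2.5 = 16.94, power 95.8%.

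The smallest N is 61, or 63 in equal groups. The stated total is reproduced before any loss. Two other options at f = 0.41 do not reproduce it: G*Power's within-between interaction at ρ = 0.5 needs only 18 in total, and a one-way ANOVA needs 96.

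**2. The Ene inputs.** d = 27 / 16.3 = 1.66. A two-sample t-test needs 11 per group at 95% power, and 11 / 0.85 = 12.9, so 13 with loss. Even 99% power needs only 15, or 18 with loss. As a plain comparison of two means, these inputs do not lead to 21.

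**3. The two effect sizes.** With three groups, the smallest f compatible with a largest difference d arises when the third mean lies midway: f = d / √6 = 1.66 / 2.449 = 0.68. In reverse, f = 0.41 allows a largest difference of at most 0.41 × √6 = 1.004 SD, and 1.004 × 16.3 = 16.4 points. So 0.41 and 27 points cannot both describe the target at SD 16.3. This step needs no assumption about ρ.

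**4. After 15% loss.** 63 × 0.85 = 53.55, about 54 (18 per group). In the calculation of step 1, λ = 54 × 0.1681 × 4 / 2.5 = 14.52 and power is 92.2%.

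| ρ | N for 95% power (equal groups) | Power at N = 54 |
|---|---|---|
| 0.3 | 48 | 97.4% |
| 0.4 | 54 | 95.1% |
| 0.5 | 63 | 92.2% |
| 0.6 | 69 | 88.9% |
| 0.7 | 75 | 85.4% |

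**5. Power for the protocol's own 27 points.** With 18 per group and d = 1.66, a two-sample t-test has 99.8% power.

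**6. What 54 evaluable participants can detect.** Progressive against constant at week 12, 18 per arm, SD 16.3, two-sided 5%:
- 80% power: d = 0.961, and 0.961 × 16.3 = 15.7 points.
- 95% power: d = 1.237, and 1.237 × 16.3 = 20.2 points.

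Baseline adjustment at an assumed ρ = 0.5 multiplies the SD by √(1 − 0.25) = 0.866, giving about 13.6 and 17.5 points.

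**7. Tested effect against planned effect.** The main effect in step 1 averages all four visits. One of them is baseline, measured before randomisation, where the groups differ only by chance. The planned model tests group by time with baseline as covariate, and the primary outcome is the contrast after 24 sessions.

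**The case against.** The strongest objection is that step 1 is a reconstruction. The between-groups option and ρ = 0.5 are not in the document, and they stand out because they return 63. Other values of ρ fit too. At 0.37 to 0.39 the same formula needs 52 or 53, and 52 / 0.85 = 61.2 or 53 / 0.85 = 62.4 rounds up to 63 in equal groups with loss properly included. At 0.4, 54 × 1.15 = 62.1 also leads to 63. A reader might infer that the 15% is certainly missing and that 95% power is certainly not reached. The documents do not support that: at correlations of about 0.4 or below, 54 evaluable participants still give 95% or more. What stands is that 0.5 is the likelier value as a default, and that the text does not show where the loss enters.

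A reader might also infer that the trial is too small. For the stated 27 points it is not (step 5). The mismatch runs in the cautious direction, since the smaller effect gave the larger sample. The shortfall at ρ = 0.5 is about 3 percentage points and treats lost participants as contributing nothing, whereas the planned intention-to-treat mixed model can use their partial data. Much lower power figures for the main comparison would have to ignore the planned baseline covariate.

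None of this reconciles f = 0.41 with 27 points, or makes the visit-averaged main effect the planned comparison.

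**Conclusion.** The sample size statement is wrong as written. Without any assumption about correlation, its two effect sizes conflict (f of at least 0.68 against 0.41; 27 points against at most about 16), and the Ene inputs, which carry the loss allowance, lead to about 13 per group and not 21.

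Conditionally on the between-groups main effect and ρ = 0.5, the 63 is the pre-loss figure, and power after 15% loss is about 92% against the stated 95%. Over ρ from 0.3 to 0.7 it runs from 97% to 85%. That test is neither the planned group-by-time model nor the primary contrast, so even the reconstructed power does not describe the primary comparison. The defect lies in the justification and the stated power; the number of participants is adequate for the 27-point target.

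**What to change.** Keep 63 participants. In the Sample size section, name the tested effect, the assumed correlation and a single effect size, and say where the 15% enters. Replace the 95% claim with what the trial delivers for its primary comparison, for example:

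> With 63 randomised and 15% loss, about 54 participants (18 per group) will be evaluable. For progressive versus constant intensity at week 12 (SD 16.3, two-sided 5%), this gives 80% power for a difference of about 15.7 FIQ-R points, or about 13.6 with baseline adjustment at an assumed correlation of 0.5. The corresponding differences for 95% power are about 20.2 and 17.5 points.

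The cost is rewording and a less favourable stated power for f = 0.41. No extra patients are needed.

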### Randomization, allocation, and blinding

We will randomize the sample to assign individuals to three groups: group 1 (progressive intensity, experimental), group 2 (constant intensity, control A), and group 3 (walking, control B). The researcher responsible for recruitment, eligibility, and evaluation, as well as the statistician, will not know which group the individual is assigned to (blinding of the evaluator and statistician). The researcher responsible for administering the exercises will only open the envelopes at the time of the intervention to identify the individual and the exercise. The researcher who will have access to the final dataset of the study will not be involved in the evaluations, randomization or intervention. The database will be set up in a restricted access link and the person responsible for the data will only communicate with the evaluator.

Once enrolled, baseline assessments will be conducted before participants are randomized (1:1:1) to three groups (progressive intensity, constant intensity, and walking) using simple randomization (via the website randomization.com) and allocation concealment, through opaque, sealed, and sequentially numbered envelopes, by an investigator who is not involved in the recruitment and treatment of participants (Fig. 1).

Sixty-three pieces of paper corresponding to the three groups will be placed in opaque sealed envelopes. All raters will be blinded to participant allocation. The therapist responsible for the interventions will not know the outcome of the evaluations and will only open the envelopes at the time of the intervention. Due to the proposed intervention (physical exercise), the therapist and participants will not be blinded to the intervention. Statistical analysis will be performed by a researcher blinded to the aims of the study. Participants will be instructed not to share information about the interventions with other participants and/or researchers.

### Outcomes

Primary outcome will be the comparison (among groups) of the effect of 24 sessions of resistance training (progressive intensity vs. constant intensity) on impact of fibromyalgia. Secondary outcomes will be to evaluate changes in sleep quality, anxiety, depression, cutaneous sensory threshold, wind-up mechanism, diffuse nociceptive inhibitory control, walking ability, musculoskeletal capacity after 24 sessions of resistance training, as well as global perceived effect and adherence regarding treatment and impact of fibromyalgia during the intervention and after 3 months of non-exercise follow-up (Fig. 2).

### Assessments

After obtaining free, prior and informed consent, we will collect information for sample characterization. As such, initial assessment, body mass, stature, waist circumference, sex, age, comorbidities, family history, medication use, education, occupation, and impact of the Covid-19 pandemic (Table 1). In addition, we will use the instruments and tests (below) to obtain the variables mentioned in the primary and secondary outcomes.

**Table 1 Tab1:** Instruments and tests to assess the participants

Outcome	Assessment (questionnaire or test)	MCID
Initial assessment	Clinical and anthropometric characteristics	n/a
Fibromyalgia screening (score)	Fibromyalgia Rapid Screening Tool [40, 41]	n/a
Impact of fibromyalgia (score)^a,b^	Revised Fibromyalgia Impact Questionnaire [42]	27
Pain level (score)^b^	Numeric Pain Rating Scale [44]	2
Sleep quality (score)^b^	Pittsburgh Sleep Quality Index [55]	n/a
Anxiety and depression (score)^b^	Hospital Anxiety and Depression Scale [57]	n/a
Cutaneous sensory threshold (score)^b^	Esthesiometry test	n/a
Wind-up (score)^b^	Temporal summation test	n/a
Diffuse noxious inhibitory controls (score)^b^	Conditioned pain modulation test	n/a
Ability to walk (m)^b^	6-Minute Walk Test	156–167
Musculoskeletal capacity (Newtons)^b^	Isokinetic dynamometer	n/a
Maximal dynamic strength for exercise load (kg)^*^	1-repetition maximum test	n/a
Global perceived effect regarding treatment (score) ^b,†^	Global Perceived Effect [65]	3

MCID: Clinically Important Minimal Difference; n/a: Not Applicable. a: Primary outcome – comparison (among groups) of the effect of 24 sessions of resistance training (progressive intensity vs. constant-intensity) on impact of fibromyalgia. b: Secondary outcome – changes after 24 sessions of resistance training, as well as the global perceived effect regarding treatment and impact of fibromyalgia during the intervention and after three months of nonexercise follow-up. *Evaluation of maximal dynamic strength for exercise load, a procedure used to adjust resistance training intensity every 4 weeks (1st, 4th, and 8th week). †Assessment of the impact of fibromyalgia, as well as global perceived effect regarding treatment (6th, 12th, and 24th week)

### Fibromyalgia screening

We will screen for fibromyalgia using the Fibromyalgia Rapid Screening Tool (FiRST) [40]. This is an instrument validated by de Sousa et al. (2022) [41] for the Brazilian population, with adequate reliability and internal consistency. It is a self-administered instrument consisting of six items with the answer options “yes” or “no”, with a cut-off score of 5 points, meaning that people who score 5 or 6 are likely to have fibromyalgia.

